## Abstract

**Background:**

The microbiota plays a key role in early immunity maturation that affects infant health and is associated with the development of non-communicable diseases and allergies in later life.

**Objective:**

The MYBIOTA is a prospective mother-infant cohort study in Malaysia aiming to determine the association between gut microbiota with infant health (temperament, gastrointestinal disorders, eczema, asthma, and developmental delays) in Selangor, Malaysia.

**Methods:**

Pregnant mothers will be enrolled in their first trimester of pregnancy, and follow-ups will be done for infants during their first year of life. Maternal-infant biological samples (blood, feces, saliva, urine, and breast milk), anthropometric, dietary, and clinical information will be collected at different time points from early pregnancy to 12 months postpartum.

**Discussion:**

This study could provide a better understanding of the colonization and development of the gut microbiome during early life and its impact on infant health.

**Clinical trial registration:**

https://clinicaltrials.gov/, identifier NCT04919265.

## Introduction

Gut microbiota plays a critical role in children's developmental pathways, especially in the first 1,000 days of life, due to the interplay between the establishment of the risks for diseases over infants' life course and infant health (1–3). Infant gut microbiota develops after birth, but the initial bacterial colonization occurs as early as when the fetus is still in the lower uterus (1). However, microbial diversity and colonization patterns vary at different time points and among infants (1, 4). More than 95% of the microbiota composition in the infant's intestinal area could be categorized into four major phyla: Firmicutes, Bacteroidetes, Actinobacteria, and Protecteobacteria (1). Two major transitions take place in the gut microbiota during infancy. The first transition characterizes the dominance of Bifidobacterium right after birth and during lactation, followed by the dominance of Bacteroidetes and Firmicutes during the weaning period, the introduction of solids foods, and continued breastfeeding practices, marking the second transition (4, 5).

Recently, increasing evidence have shown the impacts of pre-natal maternal factors on infant gut microbiota through the transmission of metabolic diseases passed from mother to child. The maternal factors are primarily associated with physical health before and during pregnancy as indicated by high pre-pregnancy body mass index (BMI) (6–8), unhealthy weight gain (6, 8), maternal exposure to medications (7–10), and gestational diabetes mellitus (GDM) (7, 8, 11). Furthermore, environmental factors involving maternal diet, including high-fat diet (7, 8, 12), smoking (10, 13), and food insecurity (14) during pregnancy are linked to the changes in infant gut microbiota. The variations in infant gut microbiota due to diet diversity among Malaysian pregnant women of different ethnic groups and the differences between Western and Eastern diets are worth investigating. Additionally, previous studies have shown that breast milk composition (4, 10, 15, 16) and maternal gut microbiota (7, 10) are linked to infant gut microbiota. Nevertheless, the composition of breast milk and gut microbiota of Malaysian women and their effects on infant gut microbiota remains unknown.

Recent discoveries have highlighted how the psychological factors of mothers, including depressive symptoms and stress, would alter gene expressions related to maternal gut homeostasis, subsequently affecting the fetal gut development and oral microbiome (17–19). However, the effects of maternal prenatal psychological factors and infant gut microbiota and immunity remain unclear. Additionally, literature on the association between maternal physical activity level and infant gut microbiota were limited to animal studies (20, 21), hence the requirement to substantiate this association *via* human studies. An extensive investigation is necessary to determine the influence of maternal pre-natal factors on infants' gut microbiome composition and diversity.

Besides pre-natal factors, accumulating studies have shown that several post-natal factors are associated with the alteration in diversity and abundance of gut microbiota in infants, including gender (22), birth order (4, 10), gestational age (4, 23), delivery mode (4, 22, 24), home settings (25), and pet rearing (24, 26, 27). Meanwhile, inconsistencies were found in associating infant growth (weight, length, and head circumference) with gut microbiota (28). Furthermore, infant feeding patterns (4, 10, 15, 22), dietary intake and diversity (29, 30) were reported as major determinants of the composition and alpha diversity of infant gut microbiota in western countries. However, despite the importance of identifying these factors, no such investigations have been conducted among Malaysian infants. Therefore, studies on infants' diets are essential due to the different dietary intake of Malaysian infants compared to those in western studies. In general, understanding the connection between pre-natal factors, post-natal factors, maternal gut microbiota, and infant gut microbiota is essential for infant health improvement and disease prevention into adulthood.

Recent studies have shown that gut microbiota is associated with temperament (31–33) and risks of gastrointestinal disorders (2, 34), eczema (35), asthma (36), and developmental delays in infants (37, 38). Temperament is a biologically-based individual differences in behavior in the form of activity, affectivity, and self-regulation, which is often used to assess a child's behaviors in early life (39). Gut microbiota influence on temperament traits warrants further inspection due to the rapid neurodevelopment at infancy (31). Thus, the current study aims to holistically understand the connection between behavior and the microbiota-gut-brain axis by studying temperament as a psychosocial variable. Furthermore, alterations in the composition and stability of infant gut microbiota lead to the development of acute and chronic gastrointestinal disorders (34). A local study showed that the prevalence of functional gastrointestinal disorders (FGIDs) among infants, including regurgitation, colic, rumination syndrome, dyschezia, functional constipation, and diarrhea, were 10.5, 1.9, 1,7, 1.3, 1.1, and 0.3%, respectively (40). Children with FGIDs were reported to have a lower quality of life, a high number of doctor visits and hospitalizations, and increased vulnerability of developing a more severe form of FGIDs and pain-related conditions in the future (41). Therefore, more research is needed to understand the association of gut microbiota and gastrointestinal disorders in infants.

Studies have shown a rapid and high diversification of gut microbiota over the first year of life in healthy children, but this is not the case for children with allergy, asthma (42, 43) and malnutrition (44). The prevalence of eczema and wheezing among Malaysian infants was 27.6 and 6.1%, respectively (45), in which the problems could be attributed to the disruption of intestinal microbiota in early life (35, 36). Besides, early life gut microbiota has been shown to be associated with the risk factor of childhood obesity, including infant's appetite traits (46). Infants who have a high abundance of the phylum Firmicutes in their gut microbiota was correlated with lower food responsiveness (46). Additionally, another study elucidated that the phylum Firmicutes was found to be abundant in the gut microbiota of obese children (47). An altered and immature gut microbiota could lead to malnutrition due to impaired energy production, vitamin biosynthesis, and immune protection (48, 49). Thus, early life intervention on immature and unstable gut microbiota is necessary to prevent the worsening of eczema, asthma symptoms, and obesity as infants grow.

Emerging evidence shows that disruption in the development of the gastrointestinal tract during the early post-natal period can affect brain development (37, 50). Impairments of developmental features relative to the child's age often refer as developmental delays (38). Poor performance on developmental domains, such as neurocognitive during childhood may affect health outcomes later in life, including poorer emotional awareness and educational attainment in later adulthood (51). The first year of life in humans is a critical period of rapid gut colonization and brain growth, but little is known about this relationship (38). Therefore, establishing a healthy gut microbiota among infants is essential to ensure optimal growth and development as well as a good quality of life.

Research on gut microbiota and the key determinants of microbial variation among Southeast Asian children remains lacking (52). Specifically, the Malaysian Working Group on Gastrointestinal Health reported a lack of research and awareness on the role of gut microbiota in early life (53). Increased awareness on the importance of gut health will help establish pre-natal and post-natal factors that promote healthy development and functioning of the immune system, gastrointestinal health, and metabolism in infants. In Malaysia, previous studies on gut microbiota mainly focused on pre-adolescent (52, 54) and pre-school children (55). While there are few local mother-infant cohort studies (45, 56, 57), none observed changes in infant gut microbiota over time.

Overall, it is essential to understand the host-microbe interactions in the first year of life since this period is crucial for infant health programming and may influence infant development with short- and long-term health consequences (1–3). The lack of evidence, especially from the Southeast Asia, calls for further studies to understand how gut microbiota in early life affects disease development (allergy, eczema, metabolic disease, and gastrointestinal disease) into adulthood. Since there is a lack of longitudinal research on infant gut microbiota in Malaysia, this cohort study aims to determine the association between gut microbiota with infant health (temperament, gastrointestinal disorders, eczema, asthma, and developmental delays) during the first year of life at different follow-ups. The specific objectives include:

To assess infant gut microbiota (composition, taxonomy, diversity, and abundance) during the first year of life.To assess temperament, gastrointestinal disorders, eczema (presence and severity), asthma (likelihood of developing), and developmental delays of infants.To determine the associations between socio-demographic, pre-natal and post-natal factors with gut microbiota in infants at 12 months.To determine the associations between infant gut microbiota and infant health (temperament, gastrointestinal disorders, eczema, asthma, and developmental delays) at 12 months.

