The rising attention of good gut health development in infants to ensure optimal child development in Malaysia (52–55) necessitates this prospective cohort study. The major contributions of this study would include the prospective cohort study design and providing clarity of temporal sequence between exposures and outcome. This study involves comprehensive and prospective quantitative assessments of mothers and infants. Besides, frequent collections of urine, feces, saliva, and breast milk samples enable a holistic assessment of maternal and infant gut microbiota over time, identifying the microbiota alterations and abundance. However, one of the limitations of this study is the multiple assessments on the pregnant women during their first, second and third trimesters until 12 months postpartum, which could be potentially burdening and lead to high dropout rates. The commitment required in the collection and delivery of bio-samples in the morning may be burdensome for working mothers. These situations will be addressed by providing incentives per visit and a summary of findings and reminders about all the follow-up activities *via* phone calls and text messages. Another possible limitation is the compliance of mothers and infant sample collections (saliva, feces, urine, and breastmilk). This limitation will be overcome using user-friendly self-collection kits with clear instructions and reminders by the researchers. Furthermore, the researchers will collect samples, thus easing the burden of respondents. Besides, there are concerns on the response and social desirability bias due to the self-report nature of the questionnaire on infant health, including temperament, gastrointestinal disorders, eczema, asthma, and developmental delays. Moreover, differences in sample handling protocols, collection procedures and processing data pipelines could be the limitation of this study.

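### Objective 4, on its natural reading, relates gut microbiota to infant health at the same 12-month visit, which cannot give the temporal sequence the article claims

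*Protocol article*

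**What the plan says.** Four places in the protocol article bear on this point.

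- **Introduction, overall aim.** The association between gut microbiota and infant health is to be studied "during the first year of life at different follow-ups".
- **Introduction, specific objectives.** Objective 1 is "To assess infant gut microbiota (composition, taxonomy, diversity, and abundance) during the first year of life". Objective 3 concerns the association of "socio-demographic, pre-natal and post-natal factors with gut microbiota in infants at 12 months". Objective 4 is "To determine the associations between infant gut microbiota and infant health (temperament, gastrointestinal disorders, eczema, asthma, and developmental delays) at 12 months".
- **Statistical analysis.** A generalized linear model, adjusted for confounders, is named for the association between microbiota and infant health. No exposure visit, lag or repeated-measures structure is given. Incidence rates of asthma, eczema and gastrointestinal disorders will be calculated, but they are not linked to microbiota at any visit.
- **Discussion.** The claimed contributions include the "prospective cohort study design and providing clarity of temporal sequence between exposures and outcome", and repeated sampling that will "enable a holistic assessment of maternal and infant gut microbiota over time".

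The Data collection timeline lists six post-natal visits, and the section on collection of samples provides feces kits at each visit.

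**The concern.** Objective 4 is the objective that answers the study's aim. If exposure and outcome are both taken at 12 months, the analysis is cross-sectional even though the cohort is prospective.

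Eczema or a gastrointestinal disorder present at 12 months may have begun before that stool was passed. Changes in feeding, or antibiotics given because of the disorder, could then have altered the stool. The Introduction itself names feeding patterns and dietary intake as major determinants of infant microbiota, so this backward route is plausible on the article's own account. An association could run in either direction, and the model could not tell which.

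The article's rationale also points to early exposure. The Introduction describes two major transitions, one after birth and during lactation and one around weaning, and it suggests that eczema and wheeze could stem from disturbance of the microbiota in early life. A 12-month stool comes late in that process.

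**Working it through.** No figure in the plan is at issue, so the check sets the passages side by side.

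1. **Visits available.** The Data collection timeline gives 3 antenatal visits (8–12, 24 and 34 weeks) and 6 post-natal ones (1–5 days, 10–15 days, 1, 4, 6 and 12 months). 3 + 6 = 9, which matches the stated total of nine. With feces kits at each visit, infant stool is available at up to 6 time points, 5 of them before 12 months.

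2. **Reading A of Objective 4: the date covers both variables.** Objective 3, one line earlier, dates the microbiota to 12 months. Carried into Objective 4, this gives 12-month microbiota against 12-month health. One of six stools is then the exposure, and it is not ordered before the outcome.

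3. **Reading B: the date covers health only.** The phrase comes directly after the list of health outcomes. In Objective 3 it also follows the outcome and cannot date the pre-natal exposures. Under this reading the outcome is at 12 months and the time of the microbiota is left open.

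4. **Against the aim.** Reading A narrows several follow-ups to one. Reading B is compatible with the aim but does not say which of the stools is the exposure.

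5. **Against the claimed strength.** Reading A cannot give temporal order for the association between microbiota and health. Reading B can, but only if the exposure stool is stated to precede the outcome, and no text says so.

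6. **Does the Statistical analysis section decide?** No. The model is given without a visit. The one-way ANOVA and PERMANOVA are also given without a time structure. The incidence rates are a separate calculation.

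Under either reading, then, Objective 4 as written does not secure the order of exposure and outcome that the Discussion claims.

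**The case against.** The strongest reply is that Reading B is grammatically sound and fits the aim, Objective 1 and the planned incidence rates, so a cross-sectional analysis is not established. That stands: the same-visit analysis is the natural reading, not the only one. It does not remove the point, because Reading B still leaves the exposure visit unstated.

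A second reply is that the Discussion's remark on temporal sequence is general and may refer to the pre-natal exposures. This is partly right. For pre-natal factors the order is clear. But the remark is not limited to them, and the study's stated aim is the link between microbiota and health.

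A third is that exposure visits and lags are detail for a full protocol or analysis plan. That would hold if the article were merely silent. Here it writes an objective whose natural meaning is at odds with its own aim.

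A reader might also infer more than the documents support:

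- **That Objective 3 is cross-sectional too.** It contains no health outcome, and it relates pre-natal and earlier post-natal factors to later microbiota. It is largely time-ordered.
- **That the five earlier stools go unused.** Objective 1 uses them to describe the microbiota over the first year. They drop out only of Objective 4, and only under Reading A.
- **That a particular number of eczema cases would have exposure measured after onset.** The eczema prevalence quoted in the Introduction comes with no age or time of onset, so no count can be derived.

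**Conclusion.** The concern holds for Objective 4. On its natural reading it is a same-visit association, which conflicts with the aim in the same section and cannot support the temporal sequence claimed in the Discussion. The model text does not resolve this.

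The effect is on interpretation: under that reading, reverse causation and an effect of microbiota on health cannot be told apart. Its size in infants cannot be given from the documents. The conclusion assumes that some disorders present at 12 months began before the 12-month stool, and that they or their management can change the stool. It does not require that most did.

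It is not established that the sponsor intends a cross-sectional analysis, and the criticism does not extend to Objective 3.

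**What to change.** - **Reword Objective 4 and the model text.** In the principal analysis of microbiota and health, take stools from earlier visits (for example 1, 4 and 6 months) as the exposure and outcomes at or up to 12 months as the response.
- **Protect the order.** Where the questionnaire schedule allows, exclude infants whose eczema or gastrointestinal disorder was reported at or before the sampling visit.
- **Adjust for what precedes the sample.** Include feeding and antibiotics before the stool. Feeding is assessed at 1, 4, 6 and 12 months. The text lists antibiotics among the items asked at recruitment, so confirm that use by the infant is also recorded.
- **Keep the 12-month same-visit association as secondary** and describe it as cross-sectional.
- **Align** the aim, Objective 4 and the temporal-sequence statement in the Discussion.

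The stools are already planned, so the change is mainly one of wording. Whether early-onset cases can be excluded depends on the visit-by-visit schedule in Figure 1, which was not available here; the Questionnaires section gives timing only for the appetite instruments. The price is fewer incident cases once early onset is excluded, and so somewhat less precision.

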## Methods and analysis

### Study design

The MYBIOTA is a prospective cohort study involving pregnant women in the first trimester (gestational age: 8–12 weeks) and their infants up to 12 months in Selangor, Malaysia. The Standard Protocol Items: Recommendations for Interventional Trials (SPIRIT) guideline (58) was used as a reference to develop this study protocol.

### Participant selection

The sample size required for this cohort study is 225 mother-infant pairs, considering the effect size of 0.427 (59), confidence level of 95%, power of 80% and attrition rate of 29.0% (45). First, the list of private hospitals in Selangor will be obtained from the Ministry of Health. Next, eight private hospitals will be randomly selected using a computerized random number generator with an estimated participation of 30 eligible pregnant women per hospital in a month. Pregnant women aged between 18 and 45 years old in their first trimester of pregnancy who visit the selected private hospitals and plan to attend post-natal check-ups for at least 1 year in the study area will be recruited. Meanwhile, pregnant women diagnosed with immune deficiency, severe allergic conditions, psychiatric disorders, multiple pregnancies, preterm delivery (<37 weeks), a newborn with congenital abnormalities, and hospitalized in neonatal intensive care unit immediately after birth will be excluded from this study.

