### Statistical analysis

The IBM SPSS Statistics software version 27 (IBM Corp., Armonk, NY, USA) will be used to analyze the data. Categorical variables will be presented in frequency and percentage, while continuous variables are presented as mean ± standard deviation (SD). The normality of continuous data will be tested using the skewness test (89). Gut microbiota will be analyzed in terms of alpha diversity, beta diversity, and differential abundance of OTUs (87). The incidence rates of asthma, eczema and gastrointestinal disorders among infants will also be calculated. Principal coordinate analysis (PCoA) plots with phylogenetic and non-phylogenetic distances will be plotted (87). One-way ANOVA with corrections (Bonferroni method) and Tukey HSD test will be carried out (89) to test for statistically significant differences in taxonomic richness, diversity measures, bacterial load, and bacterial abundances. Permutational multivariate analysis of variance (PERMANOVA) based on Bray–Curtis distances and 1,000 permutations (89) will be used to evaluate which factors are associated with the composition of the microbiota.

A generalized linear model (GLM) will be used (90) to determine the associations between predictors and gut microbiota and the association between gut microbiota and infant health after controlling for confounders. The strength and precision of each association will be determined using the relative risk (RR) with 95% confidence intervals (CI) after adjusting for potential confounders. The significance level for all statistical analyses will be set at *p* < 0.05. Meanwhile, the Bonferroni correction will be applied to counteract the effect of multiple testing and avoid multiple spurious positives (91). The alpha value will be adjusted to account for the number of comparisons performed (91).

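### The stated 225 pairs match an attrition allowance added by multiplying by 1.29; on that reading about 160 pairs remain at 12 months, with about 77% power rather than 80%

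*Protocol article*

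**What the plan says.** The sample-size statement is a single sentence under Participant selection. It gives the required size as "225 mother-infant pairs, considering the effect size of 0.427 (59), confidence level of 95%, power of 80% and attrition rate of 29.0% (45"). Besides the total, it lists four inputs: an effect size of 0.427 attributed to a cited study, a 95% confidence level, 80% power and 29.0% attrition attributed to another cited study.

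It does not give the test, the type of effect size, the number or relative size of the groups, the number needed before attrition, or how attrition was applied. The Statistical analysis section is consistent on the error rate: "The significance level for all statistical analyses will be set at" p < 0.05.

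The third and fourth specific objectives, at the end of the Introduction, concern associations at 12 months. The pairs that count for them are those still in follow-up at that age.

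**The concern.** An attrition allowance must leave the required number after the losses. If a fraction *a* of those enrolled is lost, the enrolled number is the required number divided by (1 − *a*). Multiplying by (1 + *a*) is a common slip. It always gives too few, and the gap widens as *a* grows; at 29% it is no longer negligible.

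The printed total looks like the result of that slip. This sentence is the only quantitative support for the cohort's size, and a reader will take it to mean that 225 enrolled pairs give 80% power once the expected losses have occurred.

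**Working it through.** **Inputs from the protocol article:** effect size 0.427, 95% confidence level, power 80%, attrition 29.0%, total 225 (Participant selection); significance level 0.05 (Statistical analysis).

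**Assumed, because not stated:** 0.427 is a standardised difference between two means (SD = 1), the two groups are equal in size, and the test is two-sided.

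**Step 1. Reproduce the stated figure.**
- Per group: n = 2 × (1.960 + 0.842)² / 0.427² = 86.1, rounded up to 87.
- Total before attrition: 2 × 87 = 174.
- Multiplying: 174 × 1.29 = 224.46, rounded up to **225**, the printed total.
- Dividing: 174 / 0.71 = 245.07, rounded up to **246**.

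**Step 2. Try other readings at 80% power.**

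| Reading | Base total | × 1.29 | ÷ 0.71 |
|---|---|---|---|
| Two-sided, equal groups, normal approximation | 174 | 225 | 246 |
| Two-sided, equal groups, t-test | 176 | 228 | 248 |
| One-sided, equal groups, normal approximation | 136 | 176 | 192 |
| One-sided, 2:1 groups, normal approximation | 153 | 198 | 216 |
| Two-sided, 2:1 groups, normal approximation | 195 | 252 | 275 |

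Only the first row gives 225, and only by multiplication. The exact match belongs to the normal-approximation formula; the t-test needs 87.07, hence 88 per group, and does not reproduce it. Reading 0.427 as a correlation, a paired difference or a hazard ratio gives base sizes of roughly 41 to 49. Reading it as an ANOVA effect size f with up to 10 groups gives at most about 95. None of these reaches 225. One division comes close (223, one-sided), but it needs 85% power, against the stated 80%.

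**Step 3. What 225 delivers.**
- Completers: 225 × 0.71 = 159.75, about 160, or 80 per group. This is 174 − 160 = 14 short.
- Power, normal: Φ(0.427 × √(80/2) − 1.960) = Φ(2.701 − 1.960) = Φ(0.741) = **77.1%**.
- Power, t-test with 80 per group: **76.6%**.
- Effect detectable with 80% power: (1.960 + 0.842) × √(2/80) = **0.443** (normal), or **0.446** (t-test).

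**Step 4. Check the alternative.** 246 × 0.71 = 174.7 completers, with power of about 80.6% (normal).

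**The case against.** The strongest objection is that the error is inferred. The article prints neither the formula nor the number before attrition, the nature of the 0.427 rests on a cited study that is not at hand, and an article may leave working to the full protocol. A reader might take it as established that the authors multiplied by 1.29. The documents do not go that far: they support a strong inference from an exact match, and the point is worded accordingly. On the two-group reading, however, the shortfall in Step 3 does not depend on how 225 was reached.

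A second objection is that another reading might give 225 by correct division. The Statistical analysis section reports associations as relative risks. If 0.427 were a relative risk between two equal groups (unpooled variance, two-sided 5%, 80% power), a comparator risk of 31% would need 164 pairs, or 231 after dividing by 0.71. A comparator risk of 32% would need 158, or 223. So a risk near 32% gives about 225. No such risk appears in the sample-size statement, so this reading needs an extra, unstated input and does not displace a match that uses the stated ones. It is a reason to name the test.

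A third objection is that little turns on 3 points of power in an observational cohort with many exposures and outcomes, where no single two-group comparison decides the study. That stands, and it limits the severity.

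A reader might also infer a larger loss from the exclusions that can be known only around birth ("preterm delivery (<37 weeks), a newborn with congenital abnormalities, and hospitalized in neonatal intensive care unit immediately after birth will be excluded"), since women enrol at 8–12 weeks. The article gives no rate for these exclusions and does not say whether the 29% already covers them. It therefore supports no figure for a further loss, and none is counted here.

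**Conclusion.** The point holds as a mismatch between a stated sample size and its stated power. On the only reading found that reproduces 225 from the stated inputs, the attrition allowance is too small. About 160 pairs are expected at 12 months instead of 174, power for 0.427 is about 77% instead of 80%, and the difference detectable with 80% power is about 0.44.

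This rests on three assumptions: that 0.427 is a standardised mean difference, that the two groups are equal, and that the test is two-sided at 5%. The Bonferroni adjustment planned in the Statistical analysis section is not included; it would lower power for any single comparison.

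It would be wrong to conclude that the cohort is seriously underpowered or its design unsound. The gap is about 3 points of power, and correcting the description needs no change to the design. It should be fixed, but it is not critical.

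**What to change.** Keep 225 if the size is settled, and restate the sentence under Participant selection along these lines: *225 pairs will be enrolled; about 160 are expected at 12 months after 29% attrition, giving about 77% power for a standardised difference of 0.427 (80% power for about 0.44), two-sided 5%, comparison of two equal groups.* Name the test and the type of effect size actually used. If they differ from those assumed here, give the number needed before attrition so that the total can be checked.

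If 80% power for 0.427 is to be claimed, the matching enrolment is 246 (248 on a t-test basis), which is 21 to 23 more pairs than 225.

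The first option costs one corrected sentence and a slightly less favourable power figure. The second costs the extra recruitment and follow-up.

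### The 225 pairs and 80% power appear to assume an unadjusted 5% level, while the analysis plan adjusts alpha by Bonferroni and the sample size makes no allowance for it

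*Protocol article*

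**What the plan says.** All references are to the protocol article.

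- **Participant selection** gives one calculation, with a total of 225 pairs. The inputs are given as "considering the effect size of 0.427 (59), confidence level of 95%, power of 80"%; a loss of 29% is then allowed for. It does not name the endpoint, the test, the group split or the metric of the effect size.
- **Statistical analysis** sets 5% as the general significance level, then states that "the Bonferroni correction will be applied to counteract the effect of multiple testing" and that "The alpha value will be adjusted to account for the number of comparisons performed (91"). The number of comparisons is not given. Associations are to be reported as relative risks with 95% confidence intervals from a generalized linear model.
- **Abstract, Objective** names five health domains without ranking them: "infant health (temperament, gastrointestinal disorders, eczema, asthma, and developmental delays) in Selangor, Malaysia".
- **Introduction** gives local prevalences: "The prevalence of eczema and wheezing among Malaysian infants was 27.6 and 6.1%, respectively (45"). It also lists six functional gastrointestinal disorders, from 10.5% (regurgitation) down to 0.3% (diarrhea). No prevalence is given for developmental delay.

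**The concern.** The study is sized at one significance level and will be analysed at a stricter one. Power is stated once, at a 95% confidence level, yet the analysis divides alpha by a number of comparisons that cannot be one: five health domains are named, and diversity measures and bacterial abundances are tested as well. Several of the health outcomes are also uncommon on the article's own figures, so a comparison of affected with unaffected infants would be far from balanced.

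What is at stake is how the results are read. If the 80% is taken to cover the main objective, a non-significant result for eczema, asthma or gastrointestinal disorders may be taken as evidence of no association when the study had a poor chance of finding one of the size it was planned on.

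**Working it through.** **Inputs.** From Participant selection: effect 0.427, confidence 95%, power 80%, attrition 29%, total 225. From the Introduction: eczema 27.6%, wheezing 6.1%, six gastrointestinal disorders. Assumed: 0.427 is a standardised mean difference, tests are two-sided, and m (the number of comparisons) is unknown and shown as a range.

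**1. Reproduce 225.** n per group = 2(1.960 + 0.842)² / 0.427² = 86.1, so 87. Total 2 × 87 = 174, and 174 × 1.29 = 224.5, so 225. Other readings tried miss it:
- the exact t-test (88 per group) gives 176 × 1.29 = 227.04;
- a one-sided test gives 176 or 192;
- a correlation of 0.427 gives about 53 to 58;
- dividing 174 by 0.71 gives 245.1, so 246.

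**2. Completers.** Multiplying by 1.29 does not offset a 29% loss; dividing by 0.71 does. With 225 enrolled, 225 × 0.71 = 159.75, about 160 completers instead of 174. This is a separate, smaller shortfall, so both totals are shown.

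**3. Bonferroni alone, 50:50 split.** δ = 0.427 × √(n₁n₂/(n₁+n₂)), with power from the two-sample t-test at two-sided alpha 0.05/m.

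| Completers | δ | m = 1 | m = 2 | m = 5 | m = 10 |
|---|---|---|---|---|---|
| 174 (87:87) | 2.82 | 80% | 71% | 58% | 49% |
| 160 (80:80) | 2.70 | 77% | 67% | 54% | 44% |

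This step hardly depends on what 0.427 measures. Any two-sided calculation with 80% power at 5% has a standardised signal of 1.960 + 0.842 = 2.80. At 0.05/2 the critical value is 2.241, so power is Φ(0.56) = 71%. At 0.05/5 it is 2.576, so power is Φ(0.226) = 59% (normal approximation).

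**4. Unequal groups.** This applies only if affected and unaffected infants are compared. The six gastrointestinal prevalences (reading one misprinted figure as 1.7) sum to 10.5 + 1.9 + 1.7 + 1.3 + 1.1 + 0.3 = 16.8%. That is the ceiling for any disorder if none overlap; regurgitation alone, 10.5%, is the floor. With 160 completers and d = 0.427:

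| Outcome | Split | δ | alpha 0.05 | alpha 0.01 (m = 5) | Detectable d at 80%, alpha 0.01 |
|---|---|---|---|---|---|
| Eczema, 27.6% | 44:116 | 2.41 | 67% | 43% | 0.61 |
| Any GI disorder, 16.8% | 27:133 | 2.02 | 52% | 28% | 0.73 |
| Any GI disorder, 10.5% | 17:143 | 1.66 | 38% | 17% | 0.89 |
| Wheezing, 6.1% | 10:150 | 1.29 | 25% | 10% | 1.14 |

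With 174 completers, eczema has 71% at 0.05 and 47% at 0.01.

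**The case against.** **The premises are inferred.** Participant selection states no split, test, endpoint or metric, and a journal article may leave these to the full protocol. Other readings can reach 225: a relative risk of 0.427 with equal exposure groups and an assumed reference risk of about 31–32% needs about 160 completers, and 160/0.71 = 225. That reading has a free parameter, but it shows the equal-group standardised difference is not the only possibility. Under it, or if 0.427 is an arcsine difference in proportions, the groups are exposure groups and the case splits in step 4 do not apply. This stands. A reader might infer that the plan contradicts itself on balance; it does not, because it states no balance. The Bonferroni shortfall in step 3 survives all these readings.

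**The divisor is unknown.** Defining the family is ordinary content for an analysis plan, and 0.01 is only what five domains would imply. This stands too, so adjusted power is a range. The shortfall is already present at two comparisons.

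**The outcomes are proxies.** The asthma outcome is the Asthma Predictive Index, for which no prevalence is given; 6.1% is wheezing. Temperament comes from a questionnaire score and need not involve a case split.

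**The study is not blind to large effects.** For eczema with 160 completers, an assumed 50:50 exposure split and m = 5, a relative risk of 3 has about 92% power, though a relative risk of 2 has about 51%. Reporting confidence intervals also limits the misreading of null results.

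A reader might conclude from the prevalences that no binary health outcome can reach the stated power. They do not show this: they cover only some outcomes and only one form of comparison.

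**Conclusion.** The concern holds in this form: the sample size fits an unadjusted two-sided 5% calculation, and the planned Bonferroni adjustment is not allowed for. At the planned effect, in the most favourable 50:50 case, power falls from 80% to 71% for two comparisons and 58% for five with 174 completers. It falls to 67% and 54% with the roughly 160 that the stated attrition leaves. These figures assume that the test meant by the 80% belongs to a Bonferroni family of two or more, and that attrition is as stated.

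The lower figures by outcome are conditional. They also assume that 0.427 is a standardised difference and that affected and unaffected infants are compared. They show how far power could fall and are not point estimates for the asthma or gastrointestinal outcomes.

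**What to change.** No extra enrolment is needed.

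1. Replace the single 80% statement with power or detectable effect for each main outcome. Use the alpha that will be applied (a range over the number of comparisons if the family is not yet fixed), the expected split, and the completers expected from 225 at 29% loss.
2. State which association the 80% at an unadjusted 5% refers to, with the test and the meaning of 0.427, and label the other associations secondary or exploratory. Which association that is remains the investigators' choice.
3. Correct the attrition step: either give about 160 as the expected completers, or note that 174 completers would need 174/0.71, about 246 enrolled.

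The cost is rewording the sample-size paragraph and the objectives, and a stated power that looks less favourable.
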